The aim of the PLAENTI study is to validate an MBP for the assessment of the quantity and nutritional quality of plant foods in an omnivorous diet. Accordingly, the primary objective of the validation study PLAENTI is to test whether the quantity of plant foods within the diet can be correctly estimated by measuring levels of selected urinary and blood biomarkers that are part of the MBP. A secondary objective is to test whether a difference in nutritional quality (healthful vs unhealthful) of plant foods in the diet can also be detected with the MBP. The effect of potential confounders (age, sex, physical activity, and body composition) on the precision of estimating plant food intake using the MBP will be assessed. Finally, the MBP will be determined in both 24-hour urine and spot urine samples. This will allow a comparison of the different sample types (24-hour urine collection, evening and morning spot urine, and different pools of these spot urines) to assess their reliability in reflecting dietary patterns through biomarker analysis. To address these objectives, participants received a 2-week dietary intervention with different proportions and nutritional qualities of plant foods, while urine and blood samples were collected at several time points.

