For this study, a total of 35 base menu plans with an average energy content of 2000 (SD 50) kcal were calculated with the software PRODI (version 7.2, Nutri-Science GmbH). These base menu plans were later energy-adjusted to create the menu plans for the participants as described in the following section. Each menu plan consisted of 4 meals. In total, 7 menu plans were calculated for the run-in period and 7 for each intervention arm. During both intervention weeks, the same 7 daily menu plans were used. However, the sequence of these menu plans differed between the first and the second week, resulting in a variation in the foods consumed in relation to the sampling times. This should help to test whether the MBP is robust and can correctly assign participants to their intervention based on the overall dietary pattern, rather than by single dishes.

The main metric used to calculate the menu plans was the proportion of plant food servings while adhering as closely as possible to a macronutrient ratio of 50/30/20 energy percent for carbohydrates/fat/protein. Table 1 shows the average proportions of plant foods in the final menu plans of the run-in period and the 4 arms during the intervention. The base menu plans and the definition of serving sizes can be found in Multimedia Appendix 1.

**Table 1. T1:** Proportions of plant foods in the calculated menu plans. Proportions of plant foods (in %) in the diet of the run-in and the 4 arms during the intervention by the metrics of servings, weight, and calories.

Metrics	Run-in	LH^a^	MH^b^	HH^c^	HU^d^
Proportion of plant foods of total servings (in %)	39	43	62	84	82
Proportion of plant foods of total weight (in %)	51	47	61	86	79
Proportion of plant foods of total calories (in %)	50	50	67	87	85

a LH: low proportion of healthful plant foods.

b MH: medium proportion of healthful plant foods.

c HH: high proportion of healthful plant foods.

d HU: high proportion of unhealthful plant foods.

For each meal, a time window for consumption was defined: breakfast (6 AM to 10 AM), lunch (11:30 AM to 2:30 PM), snack (10 AM to 5 PM), and dinner (5 PM to 8:30 PM). Alcohol, extra sugar, and dietary supplements were prohibited, while coffee, black tea, and green tea were limited to a total of two cups (=300 mL) per day. All participants could freely consume 100 mL of cow milk daily to add to coffee or tea.

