#### Sample Size

The MBP to be validated in this study will be developed at a later stage of the Plant*Intake* project, so it was not possible to calculate the sample size prior to submission of the project proposal. As a Williams test is performed in the main statistical analysis, this was used as the basis for a sensitivity analysis. The calculation was performed using the R package “MCPAN” (R version 4.1.0, R Core Team). The option “Type: Williams” was used. Specifically, for a 3-arm design (for the primary outcome) with n=15 per arm and expected values for the MBP of 1 (LH), 2 (MH), and 3.8 (HH), and a homoscedastic variance of 2.5, a power of 0.81 was obtained [21,44-46]. A total of 60 participants were expected to complete the study, with even distribution between the groups.

Based on experience with previous studies, including a study with low, medium, and high intake of fruits and vegetables by Watzl et al [47] and the more recent JPI FoodBAll study (Universal Trial Number: U1111-1177-1536), a dropout rate of 12% was assumed. Therefore, in order to analyze a total of 60 participants, the goal was to enroll 68 participants in total.

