#### Statistical Methods

The aim of the primary statistical analysis is to detect a trend in the MBP as a function of the proportion of healthful plant foods consumed by the participants. Here, the values of the MBP determined at visit 4 are adjusted with the baseline values from visit 2. The MBP values are compared between the interventions using the Williams test. The comparison is made for the 3 diets with different proportions of healthful plant foods (low, medium, or high). For simplicity, it is assumed that the primary outcome is normally distributed and has a homogeneous variance. The statistical hypothesis is that the primary outcome will follow a trend for the ordered categories of low, medium, and high intake of healthful plant foods. Group HH, with a high proportion of healthful plant foods in the diet, serves as a control. The following 3 average values of the MBP are assumed for the 3 intervention groups: *μ*1*, μ*2*,* and *μ*3. All intervention groups have a comparable sample size. An average different response is expected in the group with low and medium consumption compared to the high consumption (control) of healthful plant foods. The global null hypothesis is formulated as *H*0*: μ*1*=μ*2*=μ*3 versus the alternative hypothesis *H*1*: μ*3*≥μ*2*≥μ*1, with at least one strict inequality. When modeling the MBP, adjustment is made for the following potential confounding variables: age, sex, body composition (assessed by BIA), and physical activity (assessed by accelerometry). The MBP is considered to be validated if a significant monotonic trend is observed (*P*<.05).

As the main secondary analysis, mean MBP values will be compared between the HH and HU intervention arms, characterized by similar proportions of plant foods but differing in nutritional quality (healthful vs unhealthful). Group differences will first be assessed using an independent-samples *t* test, followed by linear regression models incorporating the same set of adjusting variables.

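### A significant trend across arm means would declare the panel validated, but that shows dose-response at group level, not that plant-food quantity is correctly estimated

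*Protocol article*

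**What the plan says.** The Introduction gives the primary objective as to "test whether the quantity of plant foods within the diet can be correctly estimated by measuring levels of selected urinary and blood biomarkers" that belong to the panel. The Intervention section explains why the menu order differs between the two weeks: this should help to "test whether the MBP is robust and can correctly assign participants to their intervention based on the overall dietary pattern" and not by single dishes.

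Statistical Methods sets the primary analysis as a Williams test of the baseline-adjusted panel value across LH, MH and HH, with HH as control. The null is equal arm means. The alternative is an ordering of the means "with at least one strict inequality". The verdict follows in one sentence: "The MBP is considered to be validated if a significant monotonic trend is observed" (P<.05).

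The main secondary analysis compares HH and HU means. Mixed models with variance components and intraclass correlations are planned for the urine sample types, but they do not enter the rule. Sample Size gives the planning values: "expected values for the MBP of 1 (LH), 2 (MH), and 3.8 (HH), and a homoscedastic variance of 2.5", 15 per arm, power 0.81. The Conclusion says that successful validation would enable use of the panel for objective dietary assessment in epidemiology.

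**The concern.** The aim speaks of estimating a quantity correctly. The rule asks only whether arm averages differ in the expected order. Its inputs are arm, panel value and covariates, and nothing in it refers to the size of the error with which the panel recovers intake. A panel whose mean rises truly and monotonically with plant proportion can meet the rule while individual values overlap so much that intake is poorly recovered.

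At stake is the word "validated", because the Conclusion rests the panel's later use as a dietary assessment tool on it. The rule is printed in full, so this is not a detail that an analysis plan would be expected to supply.

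**Working it through.** **Inputs (Sample Size, Statistical Methods, Tables 1 and 2).** Means 1 (LH), 2 (MH), 3.8 (HH); n = 15 per arm; alpha 0.05; the spread printed as variance 2.5 (SD 1.58); stated power 0.81; plant share of servings 43%, 62%, 84%; completers 14 + 15 + 15 = 44 in the three arms. Normality and equal variance are the protocol's own assumptions. The number of sides is not stated, so both were tried. No covariate adjustment is modelled.

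**Step 1: the plan's own figure.** Williams contrasts as a maximum of two correlated t statistics, 42 df, by simulation. Critical values are about 1.86 (one-sided) and 2.19 (two-sided).

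| Reading of 2.5 | Reference arm | One-sided power | Two-sided power |
|---|---|---|---|
| Variance | LH | 0.999 | 0.995 |
| Variance | HH | 0.999 | 0.997 |
| SD | LH | 0.891 | 0.815 |
| SD | HH | 0.912 | 0.845 |

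The stated 0.81 appears only if 2.5 is an SD, the test is two-sided and LH is the reference. With the printed variance it does not reproduce. Both readings are therefore carried forward. The HH rows give the chance of meeting the rule, since HH is the stated control.

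**Step 2: correct assignment at the same values.** With equal arm sizes the best cut-offs lie midway between the means, at 1.5 and 2.9.

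- SD 2.5: LH Φ(0.5/2.5) = Φ(0.20) = 0.579; MH Φ(0.9/2.5) − Φ(−0.5/2.5) = 0.641 − 0.421 = 0.220; HH Φ(0.36) = 0.641. Mean 0.480, so 52% are misassigned.
- Variance 2.5: LH Φ(0.316) = 0.624; MH 0.339; HH Φ(0.569) = 0.715. Mean 0.560, so 44% are misassigned.
- Guessing among three arms misassigns 2/3 = 67%.

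**Step 3: other accuracy measures.**

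- Between-arm variance: the mean is 6.8/3 = 2.267, and (1.604 + 0.071 + 2.351)/3 = 1.342. R² = 1.342/(1.342 + 6.25) = 0.18 for SD 2.5, or 1.342/(1.342 + 2.5) = 0.35 for variance 2.5.
- AUC = Φ(difference/(SD·√2)) for HH–LH, HH–MH, MH–LH: 0.79, 0.69, 0.61 (SD 2.5) or 0.89, 0.79, 0.67 (variance 2.5).
- Linear prediction of the servings share: the SD of 43, 62, 84 is 16.8 points. The correlation with the panel value is 0.417 or 0.587. RMSE = 16.8·√(1 − r²) = 15.2 or 13.6 points, against 16.8 with no panel.

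**Result.**

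| | Variance 2.5 (as printed) | SD 2.5 |
|---|---|---|
| Chance the rule is met (HH control) | over 99% | about 84–91% |
| Misassigned (guessing 67%) | 44% | 52% |
| R² | 0.35 | 0.18 |

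**The case against.** The objective does not say that quantity must be estimated per person, or to what error. The phrase about assigning participants explains the menu order and is not a listed outcome. Statistical Methods names detecting a trend as the aim of the primary analysis, and test and rule fit that aim. The Discussion calls the three-arm comparison dose-response, and the intended use is epidemiology, where separating group means has value. The Introduction also commits to assessing how confounders affect the precision of estimating intake, and supplementary accuracy measures may sit in an analysis plan that is not shown. All of this stands. It means that the absence of accuracy measures from the article is not itself a fault. It does not change the printed rule, which reaches "validated" with no reference to error, against an objective of whether quantity "test whether the quantity of plant foods within the diet can be correctly estimated".

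The planning means are placeholders, since the panel had not been developed when they were set, and covariate adjustment could reduce the overlap. That is fair, and it limits the figures to illustration.

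A reader might infer that the rule is met most of the time by any panel that fails to place most participants correctly. The documents do not support this. Such panels include one with flat means, which would meet the rule only about 5% of the time, and at the printed variance 56% are placed correctly. Nor can one say in general that arm explains less than a fifth of the variance: that holds only if 2.5 is an SD.

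**Conclusion.** The point holds as a mismatch between rule and objective. A significant Williams test supports the statement that the panel responds to the proportion of healthful plant foods at group level. It does not support the statement that plant-food quantity is correctly estimated or that participants are correctly assigned.

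In the scenario the trial was planned on, the rule would very probably be met (84% to over 99%) while 44–52% of participants are misassigned. That is better than guessing, but far from accurate. The range comes from the unresolved reading of 2.5. The figures assume normality, equal variance, known arm means and no covariate adjustment. They say nothing about how the actual panel will perform, and it would be wrong to read them as a forecast that it will misplace half the participants.

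**What to change.** Keep the Williams test as the primary analysis. Reword the sentence in Statistical Methods so that P<.05 supports only that the panel responds to the proportion of healthful plant foods at group level (dose-response).

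Base any statement that intake is correctly estimated on accuracy measures prespecified before the panel data are analysed and taken from the same samples: prediction error for plant-food proportion, three-way correct assignment, and AUCs for HH–LH, HH–MH and MH–LH, each with a 95% confidence interval. Use calibration from the earlier PlantIntake studies where it transfers to the visit 2 to visit 4 change. Otherwise cross-validate, leaving out whole participants or couples, and label the result as internal.

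A pass mark is not proposed. The documents give no basis for one, and 44 people cannot carry a strict one. Requiring a lower 95% bound above 50%, for instance, would need 29 of 44 correct, which has a probability of about 1% at 48% accuracy and 12% at 56%.

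The cost is wording and a short additional analysis, with no new data. The downside is a more modest headline claim and imprecise accuracy estimates: 1.96·√(0.25/44) = 0.148, or about ±15 points.

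### One significant Williams test with HH as control does not establish the monotonic trend, or the correct estimation of quantity, on which the panel is to be called validated

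*Protocol article*

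**What the plan says.** The Introduction states that "the primary objective of the validation study PLAENTI is to test whether the quantity of plant foods within the diet can be correctly estimated" from the panel's biomarker levels.

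Statistical Methods turns this into a test: "The MBP values are compared between the interventions using the Williams test", for the three healthful-plant arms. The null hypothesis is three equal means. The alternative is μ3 ≥ μ2 ≥ μ1 "with at least one strict inequality". The reference arm is named: "Group HH, with a high proportion of healthful plant foods in the diet, serves as a control". The expected pattern is described only against that reference: "An average different response is expected in the group with low and medium consumption compared to the high consumption (control) of healthful plant foods". The success rule follows: "The MBP is considered to be validated if a significant monotonic trend is observed", at P<.05. It carries no further condition. The order of the estimated means is not checked, LH is not compared with MH, and sidedness is not given.

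The Sample Size section reports power 0.81 for the Williams test with n=15 per arm, means 1, 2 and 3.8 for LH, MH and HH, and a common variance of 2.5. Table 1 puts plant foods at 43%, 62% and 84% of servings in the three arms.

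**The concern.** The medium arm is there to provide a gradation of dose, and the Discussion relies on the three arms for dose-response. The success rule does not use that gradation to check order. With HH as control, LH and MH enter each contrast with zero weight or with the same sign, so no contrast responds to their difference as such. The order is a premise of the alternative hypothesis, and means out of order belong to neither hypothesis.

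The word validated could therefore be attached to a panel that cannot tell 43% from 62% plant servings, or that ranks them the wrong way round. The panel is intended for later use in dietary epidemiology, where that distinction matters.

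**Working it through.** **Inputs.** n=15 per arm, planned means 1/2/3.8 and the figure 2.5 (Sample Size); HH as control and α=0.05 (Statistical Methods). Sidedness is not stated; two-sided is shown and one-sided was also run. The other mean patterns are my assumptions. Covariate adjustment is ignored.

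**Contrasts with HH as control.** A = HH − LH. B = HH − (LH+MH)/2. Pooled variance, 45 − 3 = 42 df. The simulated two-sided 5% critical value for the larger |t| is about 2.196.

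Standard errors at SD 2.5: A, 2.5×√(2/15) = 0.913; B, 2.5×√(1.5/15) = 0.791.

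**The plan's own figure.** With SD 2.5 and planned means, HH control gives 0.845. LH as reference, with contrasts HH − LH and (MH+HH)/2 − LH, gives 0.814, which matches the stated 0.81. With 2.5 as a variance (SD 1.58) power is at least 0.995 with either reference. So 0.81 fits an SD of 2.5. Among two-sided tests that need any one contrast, it fits LH rather than HH as reference. (A one-sided HH-control test needing both contrasts gives 0.822, also close.) All settings are carried below.

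**Why a reversal passes.** Swapping LH and MH leaves B unchanged. For 1/2/3.8 and for 2/1/3.8, B = 3.8 − 1.5 = 2.3, and 2.3/0.791 = 2.91 standard errors. Only A moves, from 2.8/0.913 = 3.07 to 1.8/0.913 = 1.97.

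**Probability of P<.05 (simulated, two-sided):**

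| Means LH/MH/HH | HH control, SD 2.5 | HH control, SD 1.58 | LH reference, SD 2.5 |
|---|---|---|---|
| 1/2/3.8 (planned) | 0.845 | 0.997 | 0.814 |
| 1/1/3.8 (no low–medium step) | 0.92 | >0.99 | 0.81 |
| 2/1/3.8 (medium below low) | 0.76 | 0.99 | 0.42 |
| 3.8/1/3.8 (low equals high) | 0.36 | 0.74 | 0.36 |

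One-sided testing with HH control raises every rate; 2/1/3.8 becomes 0.85 at SD 2.5. The isotonic-mean form of the Williams test with HH control gives 0.81 to 0.82 for 2/1/3.8. The achieved 14/15/15 moves the rates by no more than about 2 points.

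**Adding ordered estimated means (HH control, two-sided):**

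| Means | SD 2.5 | SD 1.58 |
|---|---|---|
| 1/2/3.8 | 0.73 | 0.955 |
| 1/1/3.8 | 0.46 | 0.50 |
| 2/1/3.8 | 0.11 | 0.04 |

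**Low–medium step.** The expected half-width of the 95% interval for MH − LH is 2.018×0.913 = 1.84 at SD 2.5, against an assumed step of 1. That interval lies above zero about 19% of the time.

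**The case against.** The Williams test is a legitimate trend test. If the order holds it keeps 5% error under the null, and Statistical Methods says the aim is to detect a trend. That stands: the fault lies in the claim attached to the test, not in the test.

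A reader might take the 92% for 1/1/3.8 as a false-validation rate. It is not. The alternative needs only one strict inequality, so LH = MH < HH lies inside it and the 92% is power. It shows how little the rule asks about the low–medium step. With LH as reference, its rate (0.81) no longer exceeds that of the planned means.

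A reader might also infer that the rule often passes non-monotone panels. The documents give no reason to expect a panel that falls from low to medium intake. The reversed shapes are assumptions, and their pass rates vary widely with shape, SD and reference arm. Nor does the weakness come only from choosing HH: with LH as reference, 2/1/3.8 still passes 42%.

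The word observed could be read as requiring ordered sample means, but the text does not say so. Means and SDs will be reported, so a reversal would be visible; the rule would still call the panel validated.

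Finally, a reader might infer that estimation error is ignored. The Introduction plans to assess how confounders affect the precision of estimating intake, and calibration or agreement statistics may properly sit in an analysis plan that is not shown. Their absence is no finding.

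**Conclusion.** The point holds in limited form and should be fixed; it does not invalidate the test or the sample. The stated rule reaches further than its test: a rejection supports HH above LH, above the LH/MH average, or both. It does not establish order, low–medium discrimination or correct estimation of quantity.

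The size is illustrative. A low–medium reversal of one unit is declared validated about 76% of the time at SD 2.5 and 99% at variance 2.5 with HH as control, and 42% with LH as reference at SD 2.5. These figures assume normal outcomes, equal variances, 15 per arm, no covariate adjustment and the mean patterns shown. The logical gap itself does not depend on SD, sidedness or reference arm.

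**What to change.** Reword the rule in three steps, before the panel results are known; the article describes the sample analyses as still to come.

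1. A significant Williams test alone is reported as: the panel separates high from lower healthful plant intake.
2. A claim of monotonic trend, or of validation for quantity, also requires estimated means ordered LH < MH < HH.
3. MH − LH and HH − MH are reported with 95% confidence intervals. Discrimination of low from medium intake is claimed only if the MH − LH interval supports it.

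The changes are to wording and to analyses of data already held. The price is a lower chance of success: under the planned means with HH control it falls from about 0.845 to 0.73 at SD 2.5, and from 0.997 to about 0.955 at variance 2.5.

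Step 2 is not enough alone. It cuts 2/1/3.8 to about 11% at SD 2.5 but still passes 1/1/3.8 about 46% of the time, so the interval in step 3 must qualify the claim. At SD 2.5 it will often be too wide to support low–medium discrimination even if the planned means are right, and the report should say so.

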### Allocation

The allocation sequence was generated by a biostatistician who was not involved in any further steps during the ongoing study and had no direct contact with the participants. Participants were randomly assigned to 1 of the 4 intervention arms with a 1:1:1:1 allocation by repeatedly using the “sample” function of the R software (R Core Team). Specifically, cluster randomization was used with clusters of different sizes. The clusters were heterosexual couples on the one hand and individual persons on the other. We randomized within waves for logistic reasons and stratified by sex to assess effects for females and males independently. The result of randomization was a sequential list of intervention arms with the corresponding study identifier of participants. The randomization plan is reproducible.

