### Statistics

#### Outcomes

The primary outcome of the study is an MBP measured in urine and blood samples from participants in the arms LH, MH, and HH at defined time points during the 2-week intervention period. The analysis metric for the primary outcome is the change in levels of biomarkers contained in the MBP from visit 2 to visit 4, considered as a combined panel value. The variables will be aggregated and described by average values and SDs.

The secondary outcome is the MBP measured in urine and blood samples at defined time points in the two arms, HH and HU. The analysis metric for the secondary outcome is also the change in levels of biomarkers contained in the MBP from visit 2 to visit 4, considered as a combined panel value. The variables will be aggregated and described by average values and SDs.

Moreover, the comparability of the biomarker levels in the different types of urine samples (24-hour urine, spot urine, and pooled spot urine) will be investigated to gain insight into the applicability of spot urine sampling in epidemiological studies. Other outcomes of an exploratory nature will also be measured. Metabolomic analyses will be performed by measuring different classes of metabolites in the urine and blood samples. For microbiome parameters, the analysis metrics are alpha diversity (number and uniformity of species distribution within a microbiome), beta diversity (dissimilarity of the composition of different microbiomes), and abundance of individual taxa in different microbiomes. The results of the FFQ will be used to characterize the participants’ habitual diet.

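### The main secondary HH–HU comparison has an unadjusted and an adjusted analysis, neither named as decisive, and visit 2 is not a listed adjusting variable

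*Protocol article*

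**What the plan says.** The protocol article, Statistical Methods, introduces the comparison thus: "As the main secondary analysis, mean MBP values will be compared between the HH and HU intervention arms". Two steps follow. The first is a t test: "Group differences will first be assessed using an independent-samples" t test. The second is regression, "followed by linear regression models incorporating the same set of adjusting variables". That set is given in the preceding paragraph for the primary model: age, sex, body composition and physical activity.

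The section on Outcomes defines the endpoint: "The analysis metric for the secondary outcome is also the change in levels of biomarkers contained in the MBP from visit 2 to visit 4", taken as one combined panel value. Baseline adjustment of visit 4 by visit 2 is described in words only for the primary analysis.

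The section on Allocation states: "We randomized within waves for logistic reasons and stratified by sex".

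The only decision rule belongs to the primary trend: "The MBP is considered to be validated if a significant monotonic trend is observed", with P<.05. No rule or alpha is attached to HH versus HU.

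**The concern.** HH versus HU is the comparison that answers the secondary objective, whether the panel detects nutritional quality as well as quantity. It will produce at least two P values, and more if the plural regression models are taken literally. With no ranking between them, the result that carries the conclusion could be chosen after both are known.

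Three further details are left loose:

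- The secondary paragraph speaks of mean panel values, while Outcomes speaks of change.
- The listed covariates omit the visit 2 value, usually a natural predictor of the visit 4 value.
- Wave, a randomisation factor, appears in neither analysis.

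At stake are the error rate of the quality claim and some precision in a comparison with 15 participants per arm.

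**Working it through.** The plan gives no power or error figure for HH versus HU, so there is none to reproduce. Its 0.81 concerns the three-arm trend and is not used here.

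**Inputs from the protocol.** HH n=15 and HU n=15 (Table 2); four covariates (Statistical Methods). **Assumptions.** Two-sided 5%; normal outcome; covariate R² from 0 to 0.7, because the protocol gives none.

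**1. Error rate.** The t test (28 df) and the four-covariate regression (30 − 6 = 24 df) were run on the same simulated data, 40,000 null trials per R².

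| R² | t test | regression | either | both |
|---|---|---|---|---|
| 0 | 0.052 | 0.050 | 0.069 | 0.033 |
| 0.1 | 0.049 | 0.048 | 0.070 | 0.027 |
| 0.2 | 0.051 | 0.049 | 0.076 | 0.025 |
| 0.3 | 0.051 | 0.051 | 0.080 | 0.022 |
| 0.5 | 0.049 | 0.050 | 0.085 | 0.014 |
| 0.7 | 0.050 | 0.048 | 0.087 | 0.010 |

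Two independent tests would give 1 − 0.95² = 0.0975. The two tests here are correlated, so the either-test rate stays below that.

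**2. How often the two disagree.** With a true 1-SD difference (15,000 trials per R²), disagreement is the either rate minus the both rate:

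- R² 0: 0.777 − 0.659 = 0.118
- R² 0.3: 0.875 − 0.705 = 0.170
- R² 0.5: 0.948 − 0.733 = 0.215

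So in about 12–21% of trials the unstated choice would settle the conclusion.

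**3. Which test is stronger.** Power at a 1-SD difference, t test against regression:

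- R² 0: 0.75 against 0.68
- R² 0.1: 0.75 against 0.73
- R² 0.2: 0.75 against 0.77
- R² 0.3: 0.75 against 0.83
- R² 0.5: 0.75 against 0.93

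The lines cross near R² = 0.15.

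**4. Detectable difference at 80% power, in SD of the analysed outcome.** The t test with 15 per arm gives 1.06. Multiplying by √(1 − R²) alone gives 1.06 × √0.7 = 0.89 and 1.06 × √0.5 = 0.75. That is too favourable, because chance imbalance in four covariates inflates the variance of the arm effect by about 4/23, or 17%. With the factor √(1 + 4/23) = 1.083 and 24 rather than 28 df (a further factor of about 1.006):

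- R² 0.3: 0.89 × 1.083 × 1.006 ≈ 0.97
- R² 0.5: 0.75 × 1.083 × 1.006 ≈ 0.82

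**5. Visit 2 as a covariate.** Let visits 2 and 4 have equal variance and correlation ρ (assumed), with a true difference of 1 SD of the visit 4 value. The change has variance 2(1 − ρ). ANCOVA leaves 1 − ρ², with 27 df and variance inflation of about 1/26.

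| ρ | t test on change | ANCOVA |
|---|---|---|
| 0 | 0.47 | 0.74 |
| 0.3 | 0.61 | 0.78 |
| 0.5 | 0.75 | 0.85 |
| 0.6 | 0.84 | 0.90 |

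ANCOVA has more power than the change score throughout this range.

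**6. Degrees of freedom.** Intercept, arm, visit 2, sex, age, body composition and activity use 7 of 30, leaving 23. Four wave indicators would leave 19.

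**The case against.** The wording first and then followed by most naturally describes an unadjusted comparison and then an adjusted one, a common sequence for a secondary outcome, and both are disclosed in advance. That stands. It also means that three stronger readings, which a reader might infer, are not supported.

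- *The plan inflates the false-positive rate.* Nothing says that either result would suffice. With one decisive test the rate is 5%, and if both were required it would be 1.0–3.3%. The 7–9% is conditional.
- *The plan leads with the weaker test.* That depends on an R² the protocol does not give. The Introduction says only that levels of some biomarkers can vary with these factors. In a within-person change, stable differences between people partly cancel. Below about 15% explained variance the t test is the stronger.
- *The analysis ignores baseline and stratification.* The endpoint is defined as change, so visit 2 enters by subtraction, and sex is in the regression. Ignoring balanced strata does not raise the t test's error. The phrase about the same adjusting variables could also be read to carry over the primary baseline adjustment, though visit 2 is not in the list it points to.

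It can also be said that ranking the two P values is a detail for a fuller plan. This has some force and keeps the point small. But the article does prescribe both tests and their order, and for the primary analysis it does state a criterion.

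Finally, a full model has a price. With four wave indicators and 19 residual df, simulated power at 1 SD was 0.65, 0.70 and 0.75 at R² of 0, 0.1 and 0.2, against about 0.75 for the t test. This stands and shapes the fix.

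**Conclusion.** The point holds as a cheap improvement to a secondary analysis. The text names no decisive analysis for HH versus HU and does not list visit 2 among the adjusting variables. The exposure is a false-positive rate of about 7–9% if either result may count, and a choice of test that would matter in roughly 12–21% of trials at a 1-SD effect (R² 0 to 0.5). The case for covariate adjustment depends on an unknown R². The case for visit 2 as a covariate does not depend on it, but does rest on the equal-variance assumption and ρ between 0 and 0.6. The need to name one analysis depends on neither. The primary trend analysis is unaffected.

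**What to change.** Before panel results exist, state that the HH–HU comparison is decided by one two-sided 5% test of the arm effect, in an ANCOVA of the visit 4 panel value with the visit 2 value, sex and the other listed covariates. The protocol describes the panel and the laboratory analysis as still to come, so this appears to be still open. Include wave economically, for example as a random effect, because wave 1 had only five participants across all arms (Study Timeline). Label the t test supportive.

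The cost is one sentence and some residual degrees of freedom: 28 for the t test against 23 before wave. If the four covariates prove uninformative, power is somewhat lower (0.68 against 0.75 at R² = 0 in the four-covariate simulation).
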